### Primary objective

To describe the long-term safety profile of secukinumab and other indicated therapies in patients with moderate to severe chronic plaque psoriasis.

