### Study design

PURE is a multinational, prospective, observational cohort study conducted in the practices of hospital and community dermatologists in Canada and Latin America (Argentina, Brazil, Costa Rica, Guatemala, Mexico, Panama) that treat patients with moderate to severe chronic plaque psoriasis. [14] Patients with moderate to severe chronic plaque psoriasis whom, prior to and independent of study enrollment, the treating physician has decided to treat with an indicated approved regimen as per standard of care in each participating country.

Patients are followed for up to 5 years from the time of enrollment. In accordance with the observational nature of the study, no assessment visits are imposed for the exclusive purpose of the study, however follow-up visits are recommended at 3 and 6 months post-baseline and every 6 months thereafter. Furthermore, any changes in the management of the patient including, but not limited to, changes in medication dose or frequency, termination of a medication or initiation of a new treatment is at the sole discretion of the treating physician and is to be recorded in the study data collection forms. At any time, patients may be withdrawn from the study by the treating physician or on the patient’s expressed choice.

There are two distinct patient cohorts in the study, those that initiate treatment with secukinumab and those that initiate treatment with other indicated and country-approved therapies as per local standard of care. Given the longitudinal nature of the study, it is anticipated that treatment cohort cross-over can occur. All patients will be followed in the study regardless of and after treatment cross-over, as long as they continue to fulfill the study inclusion and exclusion criteria. All analyses will be based on the intent-to-treat (ITT) principle even though treatment cohort may be considered as a time-dependent variable in some analyses.

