#### Outcome variables

The primary outcome variable will be the incidence of total AEs, total serious AEs (SAEs) and infections, as measured by the proportion of patients with at least one event, the mean number of events per patient, and the mean number of events per person-year of follow up. All adverse events will be mapped, based on the following hierarchy of exposures (in descending order of priority): [1] secukinumab, [2] other, [3] and non-biologic agents.

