### Statistical analyses

AEs and SAEs will be summarized for the two treatment cohorts using the total number of events, the total number of patients and percentage of patients who experienced at least one event within each body system and within each preferred term of the Medical Dictionary for Regulatory Activities (MedDRA); in these descriptive analyses, crossed-over patients (to either direction) will be described as a separate treatment cohort. Within each treatment cohort, patients experiencing the same event multiple times will be only counted once for the corresponding preferred term and body system. Relative risk/odds and incidence density rate ratio will be estimated to assess the difference between cohorts.

The levels of all physician-reported and patient-reported outcomes will be described for all visits by baseline treatment cohort; between-cohort differences will be assessed using the independent-samples t-test (or non-parametric alternative, as needed) for continuous variables and the chi-square test for categorical variables. In addition, the absolute changes in IGA, PASI, and BSA, will be described and the paired t-test will be conducted to assess the within-group change from baseline at each visit. Multivariate mixed models with repeated measures that may adjust for potential confounders will be used to assess the levels of each of these continuous parameters (IGA, PASI, BSA, DLQI, HADS, PEST, WPAI and PSD) over the five-year follow up period of the study.

For each visit, achievement of therapeutic endpoints, specifically IGA ≤ 1, IGA = 0, PASI 50, 75, 90 and 100 and DLQI ≤1 will be described with the proportion within each treatment cohort. Between-cohort differences will be assessed with generalized estimating equations. Time to achieving therapeutic endpoints, specifically IGA ≤ 1, IGA = 0, PASI 50, 75, 90 and 100 and DLQI ≤1, and the durability of response will be described with the Kaplan-Meier estimator. Between-cohort differences will be described with the log-rank test. Furthermore, Cox’s proportional hazards models that may adjust for potential confounders will be used to compare the two treatment cohorts.

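### The descriptive AE tables put both directions of cross-over in one column with no stated split at the switch, so that column can be attributed to neither therapy

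*Protocol article*

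**What the plan says.** All references are to the protocol article.

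- **Primary objective:** "To describe the long-term safety profile of secukinumab and other indicated therapies".
- **Study design:** cross-over is expected ("it is anticipated that treatment cohort cross-over can occur"), and observation goes on after it: "All patients will be followed in the study regardless of and after treatment cross-over". Follow-up is long: "Patients are followed for up to 5 years from the time of enrollment". All analyses are to be "based on the intent-to-treat (ITT) principle even though treatment cohort may be considered as a time-dependent variable in some analyses".
- **Outcome variables:** the primary outcome covers total AEs, SAEs and infections, measured as the proportion of patients with an event, events per patient and events per person-year. Attribution follows a ranking: "All adverse events will be mapped, based on the following hierarchy of exposures (in descending order of priority): [1] secukinumab", followed by two lower categories.
- **Statistical analyses:** the AE and SAE tables give the number of events, "the total number of patients and percentage of patients who experienced at least one event within each body system", and the same by preferred term. In these tables "crossed-over patients (to either direction) will be described as a separate treatment cohort". Within a cohort, a patient who has the same event repeatedly counts once for that term and body system.

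**The concern.** The third column is defined by patient, and its only membership condition is that a switch took place, in whichever direction. A patient who started secukinumab and moved to another therapy sits beside one who did the reverse. Their exposure sequences are opposite, and their reasons for switching are likely to differ. Nothing in the section separates what happened before the switch from what happened after it. The counting rule adds to this: the same event once before and once after the switch becomes one entry in the patient count.

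The primary objective is a safety profile for each therapy. A column that holds both exposures in both orders supplies neither. The Discussion presents the observation of cross-overs as a strength of the registry, yet in these tables that experience cannot be read by drug.

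**Working it through.** **The plan's own figures.** The article gives no figure for cross-over. The nearest are the precision figures for 1250 secukinumab patients, from half-width = 1.96 × √(p(1−p)/n):

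- AEs, p = 0.60: 1.96 × √(0.24/1250) = 2.7 points (stated ±3%).
- SAEs, p = 0.05: 1.96 × √(0.0475/1250) = 1.2 points (stated ±1.2%).
- Infections, p = 0.30: 1.96 × √(0.21/1250) = 2.5 points (stated ±3%).

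These reproduce after rounding and are not in dispute. They describe a secukinumab cohort of the full 1250, not a column from which switchers have been taken out.

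**The three attribution rules side by side.**

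| Section | Rule | What it leaves open |
|---|---|---|
| Study design | Intent-to-treat for all analyses; time-dependent cohort permitted | Which analyses use the time-dependent form; safety is not named |
| Outcome variables | Each AE mapped by an exposure ranking, secukinumab first | How person-time is divided; whether exposure means current or any past therapy |
| Statistical analyses | Switchers of both directions form a third cohort | Direction; period before or after the switch |

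The first rule keeps a switcher in the starting cohort, the second assigns that patient's events by exposure, and the third moves the patient to a separate group defined by something that happens after baseline. No section says which rule governs which table.

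**What the pooled column measures.** Let a be the share of the group's person-time on secukinumab, and let r_s and r_o be the event rates on secukinumab and on other therapy. The group's rate is a·r_s + (1−a)·r_o. With assumed rates r_s = 0.06 and r_o = 0.03 per person-year:

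- a = 0.2: 0.2 × 0.06 + 0.8 × 0.03 = 0.036
- a = 0.5: 0.045
- a = 0.8: 0.054

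The result moves with a, which the tables are not said to report, and it equals neither drug's rate. A patient percentage is mixed in the same way, because a patient can enter it through an event on either therapy.

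**How much secukinumab time could be involved.** Assume 1250 per cohort, complete 5-year follow-up and switching at 2.5 years, with fraction x leaving secukinumab and fraction y moving to it.

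Secukinumab person-years in the mixed group = 1250 × 2.5 × (x + y). Total secukinumab person-years = 1250 × 5 × (1 − x) plus that amount.

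| x | y | In mixed group | Total | Share |
|---|---|---|---|---|
| 10% | 10% | 625 | 6250 | 10% |
| 20% | 20% | 1250 | 6250 | 20% |
| 30% | 30% | 1875 | 6250 | 30% |
| 10% | 30% | 1250 | 6875 | 18% |
| 30% | 10% | 1250 | 5625 | 22% |

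The fractions and the switch time are assumptions; the article gives neither.

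**The case against.** The strongest reply is that switchers' AEs are not without a route to secukinumab. The hierarchy under Outcome variables maps every AE to an exposure with secukinumab first, and Study design permits a time-dependent cohort. A reader might infer that switchers' secukinumab experience is lost to the safety profile altogether. The article does not support that: the experience is unidentifiable in the descriptive tables of Statistical analyses, which is narrower. The reply is still not a full answer. The hierarchy assigns events but no person-time, although events per person-year is one of the primary measures, and the time-dependent analysis is optional and not tied to safety.

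Second, the article is a condensed account, and table layout is commonly left to an analysis plan. Silence about sub-columns would be no finding. The pooling of both directions, however, is a stated decision and can be judged as such. That all of a switcher's follow-up enters the column is an inference from the patient-level definition and the continued follow-up; the article does not say so.

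Third, one could build an example in which opposite truths give the same pooled rate. Take AE rates of 0.5 and 0.3 per person-year and a switch at year 2 of 5. The two directions then give (2 × 0.5 + 3 × 0.3)/5 = 0.38 and (2 × 0.3 + 3 × 0.5)/5 = 0.42. Equal numbers pool to 0.40 whichever drug has the higher rate. That needs the symmetry. With 400 leaving secukinumab and 100 moving to it, the pooled rate is (400 × 0.38 + 100 × 0.42)/500 = 0.388, or 0.412 with the drug rates exchanged. The general point is only that the figure is a mixture with an unreported weight.

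Finally, the study is descriptive, and setting switchers apart is a defensible way to keep mixed exposure out of the two main columns. That stands. It justifies a separate group, not the pooling of opposite sequences within it.

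**Conclusion.** The concern holds for the descriptive AE and SAE tables. The crossed-over column combines two therapies in both orders, so it cannot serve as the safety profile of either, and the secukinumab experience of switchers cannot be picked out there. The hierarchy and the optional time-dependent cohort address this in part, but they are not reconciled with the tables or with the intent-to-treat statement.

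The size of the effect cannot be computed from the article. The 10% to 30% share of secukinumab person-years rests on the assumed equal switching fractions, mid-follow-up switching and complete follow-up, and shows scale only. No claim is made that either drug's rate is biased by a known amount. The two main columns are not criticised here for excluding switchers.

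**What to change.** Replace the single crossed-over group with two: secukinumab to other, and other to secukinumab. Within each, report events and person-years before and after the switch date separately. State which rule governs which table: how the two groups fit the exposure hierarchy, how person-time is assigned under that hierarchy, and how both sit with the intent-to-treat statement. Say also how a patient who switches more than once is classified.

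No new data should be needed. Study design already has the ending and starting of treatments recorded, and time to treatment discontinuation is a listed outcome. The cost is wording and extra table columns.

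The price is precision. Using the plan's 5% SAE incidence and an assumed 10% switching from each cohort, the pooled group has 250 patients and a half-width of 1.96 × √(0.0475/250) = 2.7 points. Each direction alone has 125 patients and 1.96 × √(0.0475/125) = 3.8 points. That is a fair exchange for figures that can be attributed to a therapy, and the pooled column can be kept beside them as a total.

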The following secondary outcome variables will be used:Physician-Reported Outcomes:Change in IGA from baseline to each visit.Rate of change in IGA for the 5-year follow up duration of the study.Proportion of patients achieving IGA ≤ 1 at any point in time.Time to achieving IGA ≤ 1 during the study follow up period.Durability of effect (IGA ≤ 1).Proportion of patients achieving IGA = 0 at any point in time.Time to achieving IGA = 0 during the study follow up period.Durability of effect (IGA = 0).Change in PASI from baseline to each visit.Rate of change in PASI for the 5-year follow up duration of the study.Proportion of patients achieving PASI 100, 90, 75 and 50 at any point in time.Time to achieving PASI 100, 90, 75 and 50 during the study follow up period.Durability of effect (PASI 100, 90, 75 and 50).Change in BSA from baseline to each visit.Rate of change in BSA for the 5-year follow up duration of the study.Patient-Reported Outcomes:Change in DLQI from baseline to each visit.Rate of change in DLQI for the 5-year follow up duration of the study.Proportion of patients achieving DLQI ≤1 at any point in time.Time to achieving DLQI ≤1 during the study follow up period.Durability of effect (DLQI ≤1).Change in WPAI from baseline to each visit.Rate of change in WPAI for the 5-year follow up duration of the study.Change in the HADS score from baseline to each visit.Rate of change in the HADS score for the 5-year follow up duration of the study.Change in the PEST score from baseline to each visit.Rate of change in the PEST score for the 5-year follow up duration of the study.Distribution of responses to the HRU questionnaire at each visit.Change in HRU from baseline to each visit.Change in the PSD from baseline to each visit.Rate of change in the PSD score for the 5-year follow up duration of the study.Distribution of responses to the patient satisfaction question at each visit.Change in patient satisfaction from baseline to each visit.Proportion of patients adherent to treatment.Other Outcomes:Treatment discontinuation and durability.i.Proportion of patients discontinuing treatment.ii.Reasons for treatment discontinuationiii.Time to treatment discontinuation.iv.Prevalence and incidence of select comorbid conditions, with emphasis on comorbidities associated with psoriasis (e.g. psoriatic arthritis, diabetes, metabolic syndrome, cardiovascular disease)

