## Discussion

Post-approval observational studies are the only source of information that allows ongoing rigorous prospective surveillance for safety signals under routine clinical care and the assessment of real-world effectiveness, which are necessary for establishing the true population-based benefit-risk ratio of approved treatments. Furthermore, when conducted properly, observational studies play an important role in understanding, and possibly driving, the physician decision-making process in real-world, including but not limited to, treatment selection, titration, and discontinuation, as well as rationale behind these decisions. Finally, the collection of real-world healthcare resource utilization data allows the health economic evaluation of available treatment options which is not possible in controlled clinical trial settings. The extensive clinical, health-economic, and patient-reported outcomes collected, the long-term patient follow-up, and the large sample size of PURE will allow the assessment of all aforementioned objectives. Furthermore, the limited inclusion/exclusion criteria and the observation of treatment cross-overs and treatment changes per the discretion of the treating physician, will provide a valid representation on the real-world management of patients with moderate to severe chronic plaque psoriasis. Finally, an important strength of the PURE study is the use of standardised validated questionnaires which increases the internal validity of the findings and allows the comparison with other similar studies.

An important limitation of the current study, inherent in observational studies, is a high likelihood of bias by indication due to the fact that patients will be treated per the discretion of the physician. However, itself, the potential description of such a bias, is of interest given that would represent the clinical reality. In order to minimize the effect of this bias on the study results, pertaining to the comparison of the two treatment cohorts, multivariate statistical methods will be used.

In summary, PURE is a large, prospective, disease registry that will provide an accurate and comprehensive overview of the clinical reality of treating moderate to severe chronic plaque psoriasis in Canada and Latin America which may have direct implications for patients, caregivers, and healthcare providers on the management of the illness, as well as for policy makers when assessing available interventions.

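### For the continuous scores the listed outcome is change from baseline, but the only named visit-wise cohort test is an unadjusted comparison of levels, and adjustment in the mixed models is optional

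*Protocol article*

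**What the plan says.** **Outcomes.** The secondary list under Outcome variables (protocol article) gives, for PASI, "Change in PASI from baseline to each visit" and "Rate of change in PASI for the 5-year follow up duration of the study". For DLQI it gives "Change in DLQI from baseline to each visit". The same pair of outcomes, change and rate of change, is listed for IGA, BSA, WPAI, HADS, PEST and PSD.

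**Analyses.** The section Statistical analyses names these for the continuous scores:

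- Description: "The levels of all physician-reported and patient-reported outcomes will be described for all visits by baseline treatment cohort".
- Cohort comparison of those levels: "between-cohort differences will be assessed using the independent-samples t-test (or non-parametric alternative, as needed) for continuous variables".
- Change: absolute change is described for IGA, PASI and BSA only, and "the paired t-test will be conducted to assess the within-group change from baseline at each visit".
- Longitudinal models: repeated-measures mixed models, which are allowed but not required to adjust for confounders, "will be used to assess the levels of each of these continuous parameters". The list covers all eight scores.

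**Allocation.** The Discussion acknowledges "a high likelihood of bias by indication due to the fact that patients will be treated per the discretion of the physician". It then says, in firm terms, that multivariate methods will be applied to the comparison of the two cohorts.

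**The concern.** The listed outcome and the named between-cohort test do not match. For none of the eight scores does the section state a between-cohort analysis of change. For DLQI, WPAI, HADS, PEST and PSD it names no analysis of change at all.

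The mismatch matters because the cohorts are formed by physician choice. If patients starting secukinumab enter with higher or lower scores than the others, part of that gap will still be present at follow-up. An unadjusted test of follow-up levels then mixes the entry difference with any difference in response. The paired tests do not help, because finding a significant change in one cohort and not in the other is not a comparison of cohorts. The baseline score of each scale is collected, since the outcome measures are assessed at every visit and Baseline is a visit, but no named analysis is required to use it as a covariate.

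**Working it through.** **The plan's own figures.** The article gives no power or precision figure for these scores. Its only such figures, under Sample size considerations, concern adverse events. They reproduce closely (for example, an odds ratio of 1.30 from 60% with 1250 per cohort gives 88.5% power against the stated 90%) and have no bearing on this point.

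**Inputs.**

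- From the article: n = 1250 per cohort.
- Assumed, because the documents do not give them: entry gap d = 0.1 to 0.3 SD; baseline/follow-up correlation ρ = 0.3 to 0.7; equal SD at both times; no true treatment difference; two-sided 5% test; everyone attends.

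**Model.** In SD units, follow-up = ρ × baseline + error, the same in both cohorts.

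- Difference in follow-up level: ρd. Its standard error is √(2/1250) = 0.04, so z = ρd/0.04.
- Difference in raw change: (ρ − 1)d. The SD of change is √(2(1 − ρ)), so |z| = (1 − ρ)d/(0.04√(2(1 − ρ))).
- Rejection probability: Φ(z − 1.96) + Φ(−z − 1.96).

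| d | ρ | Level bias (SD) | z | Level test rejects | Change bias (SD) | Change test rejects |
|---|---|---|---|---|---|---|
| 0.1 | 0.3 | 0.03 | 0.75 | 11.7% | −0.07 | 31.6% |
| 0.2 | 0.5 | 0.10 | 2.50 | 70.5% | −0.10 | 70.5% |
| 0.3 | 0.7 | 0.21 | 5.25 | 99.9% | −0.09 | 82.8% |

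Over the whole grid the level test rejects in about 12% to 99.9% of studies, against a nominal 5%. With 800 attending per cohort (standard error 0.05), the three rows become 9.2%, 51.6% and 98.7%.

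**Raw change is not the cure.** Over the same grid an unadjusted t-test on change is biased in the opposite direction, by −0.03 to −0.21 SD, and rejects in 16% to 99% of studies. The cause is regression to the mean: the cohort that enters worse falls further without any treatment difference. A comparison conditioned on the baseline score has no bias in this model and rejects in about 5%.

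**Limit of the model.** If the entry gap reflected a stable difference that persisted in full, the level test would reject in 70.5% of studies at d = 0.1 (z = 0.1/0.04 = 2.5) and 99.9% at d = 0.2 (z = 5.0). Baseline adjustment would then leave d − ρd = (1 − ρ)d, for example 0.10 SD at d = 0.2 and ρ = 0.5. Conditioning on baseline therefore removes the part of the gap carried by the score itself, not all confounding.

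**The case against.** Several points on the other side stand.

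- **Not every comparison is on levels.** PASI 50/75/90/100 are defined against each patient's own baseline, and the article compares them between cohorts by generalized estimating equations, log-rank tests and Cox models. This covers PASI responder status. IGA ≤ 1, IGA = 0 and DLQI ≤ 1 are absolute thresholds, and no responder endpoint is listed for BSA, WPAI, HADS, PEST or PSD.
- **A model of levels can yield change.** If baseline is one of the repeated responses, the cohort-by-visit terms give the difference in change. The text does not exclude this, but does not state it either. Fitted without a constraint on baseline, and with complete data, that contrast is the difference in raw change, which has the bias shown in the working.
- **Multivariate methods are promised.** The Discussion does say so. Statistical analyses only permits adjustment, the baseline score is named in neither place, and the visit-wise t-test remains unadjusted under both.
- **The comparisons are exploratory.** The objectives are all descriptive, and Sample size considerations calls between-cohort comparisons descriptive or exploratory, in its text on adverse events. That lowers the stakes, but does not remove bias from a test the plan names.
- **Covariates may sit in an unseen analysis plan.** A bare list of confounders would properly be left to it. Here, though, the article itself fixes a test that does not match its own outcome list.

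A reader might go further and infer that the cohorts are compared only on follow-up levels, or that the plan will read an entry difference as a treatment effect. The documents do not support either. Baseline-relative comparisons exist for PASI, baseline levels will appear beside later ones in the visit tables, and nothing says how a level difference will be interpreted.

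**Conclusion.** The point holds for the continuous scores. Change from baseline is listed for all eight, no between-cohort analysis of change is stated for any of them, and the visit-wise test that is stated is open to bias from entry differences that the article itself leads one to expect. Optional adjustment in Statistical analyses and firm adjustment in the Discussion also need to be reconciled.

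The possible size is 0.03 to 0.21 SD of bias and about 12% to 99.9% rejection with no true effect. This illustrates what the test would do under the assumed gaps and correlations. It is not an estimate for this registry, because the documents give neither quantity and the range is correspondingly wide. These are secondary, exploratory outcomes, so this is a change that should be made, not a flaw in the primary safety objective.

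**What to change.** In Statistical analyses:

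1. Make the between-cohort analysis of each continuous score the repeated-measures mixed model already planned. Use post-baseline scores as response; include cohort, visit and cohort-by-visit; and make the baseline score of the same scale, with its visit interaction, a mandatory covariate. With the baseline score held fixed, the cohort contrast at each visit is also the baseline-adjusted contrast in change.
2. Turn the optional adjustment ('may') into a commitment ('will'), so that it agrees with the Discussion.
3. Keep the per-visit levels and the paired changes as description, without between-cohort p-values.
4. Do not replace the level test with an unadjusted t-test on change.

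**Cost.** Wording only; the scores are already collected. Patients without a baseline score do not contribute to the adjusted contrast, and confounding not captured by the baseline score remains, so the results should still be presented as exploratory.

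### Per-visit t-tests on the patients seen at each visit can bias late change and cohort differences in either direction; the planned mixed model should supply those estimates

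*Protocol article*

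**What the plan says.** The Statistical analyses section of the protocol article sets out three analyses of the continuous scales.

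- Within cohort, for the absolute changes in IGA, PASI and BSA: "the paired t-test will be conducted to assess the within-group change from baseline at each visit".
- Between cohorts, at all visits: "between-cohort differences will be assessed using the independent-samples t-test (or non-parametric alternative, as needed) for continuous variables".
- Over the five years, for IGA, PASI, BSA, DLQI, HADS, PEST, WPAI and PSD: "Multivariate mixed models with repeated measures that may adjust for potential confounders will be used to assess the levels" of each.

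The section does not say which result leads if a t-test and the model disagree. Change from baseline to each visit in IGA, PASI and BSA is a listed secondary outcome (Outcome variables). The only test named for it is the paired t-test.

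Study design sets the follow-up conditions: "Patients are followed for up to 5 years from the time of enrollment"; "no assessment visits are imposed for the exclusive purpose of the study"; and "At any time, patients may be withdrawn from the study by the treating physician" or by the patient's own choice. It also says that patients stay in follow-up after switching treatment, as long as they still meet the eligibility criteria, and that all analyses follow the intent-to-treat principle.

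**The concern.** A paired t-test needs both the baseline value and the value at the visit. A two-sample t-test needs the value at the visit. The recommended schedule has 11 post-baseline visits (months 3 and 6, then every 6 months from 12 to 60). With voluntary attendance and free withdrawal, the set tested in years 3 to 5 will be smaller than the enrolled cohort and may be selected by how well patients are doing. The optional non-parametric alternative has the same limitation.

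Long-term effectiveness is the first secondary objective. If attendance depends on disease control, the observed mean change drifts over time even when no patient's condition changes. If that dependence differs between cohorts, two equally effective cohorts look different, or a real difference is masked. With 1250 patients per cohort, even a modest artefact can reach nominal significance.

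**Working it through.** **Inputs from the article:** 1250 patients per cohort; baseline plus 11 visits to month 60. The article states no attrition rate, attrition mechanism or bias figure, so there is nothing of its own to reproduce.

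**Assumed inputs:** PASI-like score with baseline mean 15 and SD 5; true change -10 in both cohorts, so the true cohort difference is 0; 80%, 60% or 40% of patients retained at year 5. In cohort A the log-odds of leaving change by 0.35, 0.7 or -0.7 per SD of worse score. In cohort B drop-out is random. Each scenario was run 200 times.

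**Identity.** With π the proportion observed, observed-case bias = (1 - π) × (mean among observed - mean among unobserved). A paired change of -10.46 at π = 0.60 is a bias of -0.46, so observed and unobserved patients differ in mean change by -0.46 / 0.40 = -1.15 points. At π = 0.80 and 0.40 the implied gaps are -0.20 / 0.20 = -1.0 and -0.78 / 0.60 = -1.3.

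**Year-5 results at 80 / 60 / 40% retained.** The model is the maximum-likelihood repeated-measures estimate with unstructured covariance.

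| Drop-out depends on | Slope | Paired change, A | Model change, A | Observed difference, A - B | t-test p<0.05 | Model difference |
|---|---|---|---|---|---|---|
| last recorded score | 0.35 | -10.12 / -10.26 / -10.40 | -10.01 / -10.00 / -10.00 | -0.21 / -0.56 / -0.92 | 14 / 56 / 83% | 0.01 / -0.01 / -0.01 |
| last recorded score | 0.7 | -10.20 / -10.46 / -10.78 | -9.99 / -10.01 / -10.01 | -0.44 / -0.97 / -1.59 | 52 / 96 / 100% | 0.01 / -0.02 / 0.01 |
| last recorded score | -0.7 | -9.78 / -9.52 / -9.22 | -9.99 / -9.99 / -10.01 | 0.44 / 0.95 / 1.59 | 54 / 96 / 100% | 0.02 / -0.02 / 0.00 |
| current, unrecorded score | 0.7 | -10.24 / -10.51 / -10.88 | -10.10 / -10.21 / -10.40 | -0.49 / -0.99 / -1.74 | 64 / 97 / 100% | -0.11 / -0.21 / -0.42 |

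**Hand check of one rejection rate.** At 60% retained there are 0.60 × 1250 = 750 patients per cohort. Standard error = 5 × √(2/750) = 0.258. The ratio is 0.97 / 0.258 = 3.76, and the chance of exceeding 1.96 is Φ(3.76 - 1.96) = Φ(1.80) ≈ 96%, as simulated.

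**A second simulation on other assumptions** used baseline PASI about 15, 65% responders, and drop-out per visit interval of 3% when the last PASI was below 5 and 12% otherwise. True change at month 60 was -10.2, change among attenders -11.2, and model estimate -10.2. With 8% or 16% drop-out of poor responders, change among attenders was -10.8 or -11.6. With identical therapies and poor responders leaving at 5% versus 12% per interval, the month-60 t-test showed a false difference of 1.0 point, with p<0.05 in all 300 runs. The model difference averaged 0.01. That last setting is demanding: after 11 intervals, 0.95^11 = 57% versus 0.88^11 = 25% of persistent poor responders would remain.

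**The case against.** The strongest reply is that the safeguard is already in the plan. The mixed model covers every scale given a paired t-test, and a model of levels over time can yield visit means, changes and cohort contrasts; nothing in the section rules that out. The Discussion adds that multivariate methods will be used for the cohort comparison, although it has bias by indication in mind rather than attrition. This stands as far as it goes. It makes the remedy cheap, but it does not correct t-test results that the plan says will be produced visit by visit.

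Second, a missing-data rule may exist in the full protocol or analysis plan. That is so, and its absence from an article is not held against the plan. The point concerns the choice of test that the article does fix, and it is conditional on no imputation.

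Third, patients are followed after switching treatment, so treatment failure need not mean leaving the study. This weakens the case for heavy selection. It does not cover withdrawal, missed visits, or patients who stop meeting the eligibility criteria.

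Fourth, these are secondary outcomes in a registry whose objectives are all descriptive. That limits the stakes. The article's wording that comparisons are exploratory is, however, written about adverse events, and significance tests are planned for effectiveness.

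A reader might also infer that improvement will be overstated. The documents do not support that: they give no attrition mechanism, and the sign reverses if well-controlled patients stop attending (slope -0.7 above). Nor do they support the inference that the mixed model would eliminate the bias. It does so only when drop-out depends on recorded values and the model is suitable; the last row of the table shows what can remain.

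**Conclusion.** The point holds as a conditional one. The per-visit t-tests are a weaker choice than the model planned beside them, because they are exposed to outcome-related attrition in a long follow-up with voluntary visits.

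On the assumed attrition, the bias in change is roughly 0.2 to 1 PASI point (0.1 to 0.4 with weak selection, up to 1.4 in the harshest setting of the second simulation). This is small against a true change of about 10, so a conclusion of large improvement would survive. The cohort comparison is more fragile: a spurious difference of 0.4 to 1.6 points (0.2 to 0.9 with weak selection) when the true difference is zero. That artefact needs selection to differ between cohorts; equal selection in equally effective cohorts would largely cancel.

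When drop-out depends on the last recorded score, the model difference stays within 0.02 of zero. When it depends on the unrecorded score, 0.1 to 0.4 points remain at slope 0.7. These sizes rest on assumed scores, retention and drop-out rules, and on an unstructured covariance that the article does not specify. They show what could happen in this registry and do not predict it.

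**What to change.** In Statistical analyses, make visit-specific contrasts from the planned repeated-measures mixed model the main source for change from baseline and for the cohort difference at each visit, with 95% confidence intervals. Specify visit as categorical, cohort, and cohort by visit; add baseline value by visit for the cohort contrast, together with the confounder adjustment the plan already allows for. Keep observed means and any per-visit t-tests as description only, and print the number of patients assessed at each visit beside them.

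The cost is wording: the model is already planned and no new data are needed. The downside is reliance on the model and on a missing-at-random assumption. A sensitivity analysis that shifts the values of unobserved patients over a stated range would show how far the conclusions depend on it.
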